## Device Specific Considerations

Novadaq Stryker Spy Elite will be used, specifically model number LC3000. This device is regulated by FDA code 21 CFR § 892.1600. Exposure to the imaging device is limited to less than five minutes. Measurement usually takes a couple of minutes, and it is used after ICG IV administration. Measurements will be done only once to patients.

Software for measurement includes CINEVAQ 2.0 or newer, contained in the SPY Elite device. This allows for an interface for image acquisition, processing and controls of the device.

# TREATMENT PLAN

## Dosage and Administration

| **Regimen Description** | | | | | |
| --- | --- | --- | --- | --- | --- |
| *Agent* | *Premedication; Precautions* | *Dose* | *Route** | *Schedule* | *Cycle Length* |
| Indocyanine green | none | 5.0 mg | IV | During surgery | Single injection; may be repeated to maximum dose of 2mg/kg |
| **Specify route of administration (e.g., IVB, IVP, IVCI, PO, intra-arterial, peritoneal, intrathecal, intracavity, etc.) and duration (e.g., IVP over 10 seconds), including any allowable time windows (+/- minutes).* | | | | | |

Repeated doses of ICG could be considered if the initial dose does not create adequate uptake in reference tissue when creating a baseline to then compare with the cut edge of the pancreas. Adequate uptake will be defined as a change of ICG detected by the Spy Elite+ device when compared to tissue before ICG administration. Repeated doses of ICG injections while staying under the maximum dose would not significantly increase risk for adverse reactions. However, requiring additional doses of the dye could increase total operative time. Impact of operative time with use of ICG is further addressed in 6.1.8. “ADMINISTRATION”.

## Concomitant Medication and Supportive Care Guidelines

Supportive measures for optimal medical care are to be given throughout the study as indicated by the treating physician’s assessment of the participant’s medical need and institutional and general medical guidelines for the care of participants undergoing pancreaticoduodenectomies or distal pancreas resections.

Medications required to treat AEs, manage cancer symptoms, concurrent diseases and supportive care agents, such as pain medications, anti-emetics and anti-diarrheals are allowed in general. The participant must be told to notify the investigational site about any new medications begun after the start of the study treatment.

All medications (other than investigational products) and significant non-drug therapies (including vitamins, herbal medications, physical therapy and blood transfusions) administered during the study must be listed on the case report form (CRF).

Treatment recommendations described in the following sections may be modified according to institutional standards and guidelines as appropriate.

## Precautionary Medications, Treatments, and Procedures

To the extent possible haloperidol, heparin, nifedipine, nitrofurantoin, phenobarbital and primidone are to be avoided because of their effects on ICG pharmacokinetics.

## Prohibited Medications, Treatments, and Procedures

Active vasopressor requirement during administration will be considered in final analysis and potential exclusion, however no specific medications, treatments, or procedures are considered “prohibited” for the purposes of this protocol.

# STUDY PROCEDURES/EVALUATIONS AND SCHEDULE

## Study-Specific Procedures

- - 1. Medical history

A medical history will be obtained by the investigator or qualified designee. In addition to collecting information on demographics, the medical history will include all active conditions, and any condition diagnosed within the prior 10 years that are considered to be clinically significant by the Investigator. Details regarding the participant’s malignancy, when applicable, will be recorded separately and not listed as medical history (e.g., date of diagnosis, staging).

- - 1. Disease Assessment

The investigator or qualified designee will obtain prior and current details regarding the participant’s pancreatic pathology.

- - 1. Medication review

A complete medication history will be acquired concurrent with medical history.

- - 1. Physical examination

Physical exams must be performed by a medically qualified individual such as a licensed physician, Physician’s Assistant, or Advanced Registered Nurse Practitioner as local law permits and per institutional standards. The physical examination to be conducted will include an evaluation of: general appearance; head, ears, eyes, nose, and throat; neck; skin; cardiovascular system; respiratory system; gastrointestinal system; lymphatic system, musculoskeletal system, and nervous system. All other physical exams after baseline will include an evaluation of any AEs, or any previously reported symptoms, or prior physical examination findings. All physical examinations will also include:

Vitals to be collected include blood pressure (BP), heart rate (HR), temperature, and oxygen saturation by pulse oximetry. As part of screening/baseline visit, vitals should be obtained prior to the surgery. Vitals will also be obtained during surgery and administration of ICG.

Significant findings that were present prior to the signature of the informed consent must be included in the Medical History eCRF page. Significant new findings that begin or worsen after informed consent must be recorded on the Adverse Event eCRF page.

Height will be collected at screening only. Weight will be collected at each in person visit.

Performance status (Eastern Cooperative Oncology Group) will be determined for all participants at screening.

- - 1. Radiographic or other imaging assessments

Conventional imaging for staging of pancreatic malignancy will be performed to all screened patients. During ICG administration, the NOVODAQ Spy+ Elite Platform will be used to capture reference and pancreatic perfusion, utilizing platform software.

- - 1. Adverse event evaluation

Toxicities and adverse experiences will be assessed using the [NCI CTCAE 5.0](http://ctep.cancer.gov/protocolDevelopment/electronic_applications/ctc.htm). Safety will be monitored by assessing physical examination, vital signs, body height (screening only) and weight as clinically indicated. Additionally, hematology, chemistry, coagulation, urinalysis, thyroid function, and pregnancy will be assessed as clinically indicated.

Adverse events will be monitored from the time the participant receives treatment on study. Participants will be instructed to report all AEs during the study and will be assessed for the occurrence of AEs throughout the study, including and up to 30 days. Due to the known excellent safety profile of ICG, AEs grade 1-2 will not be collected during the study. AEs Grade 3 or higher must be recorded on the source documents and eCRFs regardless of the assumption of a causal relationship with the study drug.

Abnormal laboratory values will only be recorded as an AE if determined to be clinically significant by the investigator.

- - 1. Counseling procedures

As the impact of ICG perfusion is yet unknown with respect to clinical outcomes, results will be provided to the participants as an aggregate of overall outcomes when the study is analyzed. Individual patient measurements will be used for research purposes only and patients will be apprised of this condition during the consent process.

- - 1. Assessment of participant-reported outcomes

A survey will be answered by registered nurses, technicians and surgeons after the surgery to better understand subjective assessments of ICG use concomitant with Spy Elite platform and software.

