## Study Rationale

Current methods of evaluation for poor tissue perfusion are not ideal. Surgeons rely on visualization of the pancreatic remnant and assessment of the color and texture of the pancreas. Recently use of ultrasound has aided as another measure for tissue perfusion. However, ultrasound is operator-dependent by nature and does not provide an objective parameter. Studies show poor correlation of visual data surgeon gathers and actual tissue perfusion.

Our hypothesis is that remnant pancreas perfusion will be easily and objectively evaluated with intravenous ICG followed by imaging.

- - 1. Known Potential Risks

An immediate risk that would be presented to patients with ICG administration is exposure to an agent that could cause an adverse reaction even if there is no previous personal history of it. Overall adverse reaction to systemic ICG is estimated to be around 5% with only 0.05% as serious adverse reactions.^23, 24^ The most common adverse reactions include nausea, extravasation of ICG and urticaria. As per FDA drug insert, anaphylaxis has been reported with use of ICG. Less than 10 confirmed cases of anaphylaxis by ICG under general anesthesia are available in current literature.^25^ Addition of ICG to a surgical procedure seems to add neglible risk for adverse effects to the baseline risk of the surgery itself.

- - 1. Known Potential Benefits

Potential benefits include the possibility of detecting low perfusion tissue during surgery

Long range potential benefits: if ICG uptake correlates with pancreatic remnant perfusion, critical information for avoiding hypoperfusion will be available for clinical decisions. This study aims to investigate the relationship between hypoperfusion in surgery and postoperative leak development. Currently, no measurable, modifiable intraoperative intervention is known to decrease leak rates. Our long-range goal is carrying forward a positive outcome from this study into a clinical trial evaluating improving remnant gland perfusion and whether this may decrease postoperative fistulae.

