# STUDY DESIGN

## Description of the Study Design

*Refer to* Section 11*, Statistical Analysis for additional information regarding statistical methods used in this study.*

This is a Phase II study to assess diagnostic parameters of hypoperfused pancreatic cut edge via ICG and its relation to fistula formation versus conventional measurements. The study design consists of a single arm intervention group (n=50).

The trial will commence with the enrollment of the fifteen patients, after these 15 casesa logistics run-in of the OR ICG technique and timing will be done. During the logistics run-in, the PI will evaluate team satisfaction and measurement outcomes. This will be done through the application of a 3-question paper-based quality survey, attached in the supporting documents for the protocol. If an average score below 50% is given, study will be terminated to avoid negative impact on the logistics of pancreatectomies. Survey scores are calculated depending on the answer given, A= 0% B = 16.5% C = 33%. Minimum score 0 maximum score 100. Progressive study enrollment will continue throughout the adjustments, and enrollment will be halted if any major concerns arise. If the interim analysis does not result in study termination, enrollment of the remaining participants will resume to enroll a total of 50 patients completing study intervention and follow-up.

Aside from interim analysis evaluating logistics. A patient safety analysis will be performed at the same time. Herein, potential factors of the clinical trial that could negatively impact patient outcomes will be addressed. These factors include adverse effects of ICG administration and factors from the clinical trial process that negatively impact the conventional treatment course of patients. If any concerns are identified on interim safety analysis, the study could temporarily pause enrollment until the issues are addressed. This is to supplement study stopping rules delineated in 9.6 and Data and Safety forms.

The study schedule will be divided into 2 periods: (1) the intra-surgical period which starts at the time of ICG injection and ends when the surgical procedure is terminated and (2) the postoperative period which begins at the end of surgery and ends 30 days postoperatively.

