We will use a cutoff of 60% of the maximum ICG uptake to consider cut edge as poorly perfused. (100% measured 4-6 cm from the cut edge of the pancreas point 5 and 6 in the figure below). Additionally, to compare with non-pathologic gastrointestinal tissue perfusion, ICG uptake metrics will be captured from the gastric body.

[figure not shown]

At the completion of the proposed study, the expected outcomes are to have evaluated the safety and efficacy of intra-operative ICG administration in the assessment of pancreatic perfusion at the cut edge.

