## Time Period And Frequency For Event Assessment And Follow-Up

The occurrence of an UP, AE or SAE may come to the attention of study personnel during study visits and interviews of a study participant presenting for medical care, upon review by a study monitor, or during an audit. All AEs grade 3 or higher but not meeting the criteria for SAEs will be captured on the appropriate CRF. AEs of grade 1 and 2 will not be captured due to the well-characterized side effect profile of ICG for other indications, including IV ICG injection which is FDA approved. Information to be collected includes event description, time of onset, clinician’s assessment of severity, seriousness, expectedness, relationship to study product (assessed only by those with the training and authority to make a diagnosis), and date of resolution/stabilization of the event. All AEs grade 3 or higher occurring while on study must be documented appropriately regardless of relationship. All AEs will be followed to adequate resolution.

Any medical condition that is present at the time that the participant is screened will be considered as baseline and not reported as an AE. However, if the study participant’s condition deteriorates at any time during the study, it will be recorded as an AE after treatment with study intervention begins.

Changes in the severity of an AE will be documented to allow an assessment of the duration of the event at each level of severity to be performed. AEs characterized as intermittent require documentation of onset and duration of each episode.

At each study visit, the Investigator will inquire about the occurrence of AE/SAEs since the last visit. Events will be followed for outcome information until resolution or stabilization.

The Investigator will record all reportable events with start dates occurring after treatment with study intervention begins for 30 days after date of surgery. AEs will be evaluated using the current version of the [CTCAE v5.0](https://safetyprofiler-ctep.nci.nih.gov/CTC/CTC.aspx). At each study visit, the investigator will inquire about the occurrence of AE/SAEs since the last visit. Events will be followed for outcome information until resolution or stabilization. Any SAE that occurs after treatment with alternative therapy will be reported only if the Investigator or current treating physician has assessed the SAE as related to the study treatment.

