## Description of Statistical Methods

- - 1. General Approach

Descriptive statistics will be used to summarize patients’ baseline characteristics and baseline disease characteristics. This information will be presented with percentages, means with standard deviations median and range as suitable. Inferential tests will use a null-hypothesis significance testing of <0.05.

- - 1. Analysis of Primary Endpoint(s)

*11.4.2 Primary endpoint – Leak rate*

We will assess the association between ICG perfusion and leaks using a chi-square test. Logistic regression analysis will be further utilized to evaluate covariates influencing the presence/absence of leaks, with specific attention to the predictive value of percent maximum perfusion metrics and time to maximum metrics at the set timepoints in the protocol. Refer to Sections 3.1 for additional information

- - 1. Analysis Of The Secondary Endpoint(S)

*11.4.3.1 Secondary endpoint –*

We will use descriptive statistics to summerize the grade of leasks and ICG metrics.

*11.4.3.2 Secondary endpoint – ICG logistics*

The results of the survey to be applied to surgeons and other OR staff will be summerized using a descriptive statistics.

- - 1. Safety Analyses

Adverse events will be tabulated by the Medical Dictionary for Regulatory Activities (MedDRA Version 21.1) preferred term and system organ class. The severity of the AE will be assessed by National Cancer Institute (NCI) Common Terminology Criteria for Adverse Events (CTCAE) version 5.0. Using the safety analysis set, descriptive statistics will be used to summarize all on-study AEs, grade 3-4 AEs, treatment-related AEs, grade 3-4 treatment-related AEs, SAEs, treatment-related SAEs, and AEs leading to study therapy discontinuation. Grade 3-4 laboratory abnormalities will be summarized using worst grade NCI CTCAE v5.0 criteria.

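### The rule against collecting grade 1-2 adverse events conflicts with the planned interim review of ICG effects, the stated ICG safety outcome and the planned AE tables

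*Protocol*

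**What the plan says.** The collection rule appears twice. Protocol section 7.0.5 (Adverse event evaluation) says "Due to the known excellent safety profile of ICG, AEs grade 1-2 will not be collected during the study", and section 9.4 says "AEs of grade 1 and 2 will not be captured", on the ground that the side effects of ICG are well characterized in other indications. Events of grade 3 or higher are recorded whatever their cause, and SAEs are defined by outcome in section 9.1.1.

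Four other places presuppose a wider record:

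- Section 2.0 plans a patient safety analysis alongside the 15-case run-in. Of the factors it will examine, it says "These factors include adverse effects of ICG administration".
- The same section says "the expected outcomes are to have evaluated the safety and efficacy of intra-operative ICG administration".
- Section 10.3.3 says "descriptive statistics will be used to summarize all on-study AEs". It then lists grade 3-4 AEs, treatment-related AEs and grade 3-4 treatment-related AEs as separate summaries.
- Section 7.0.3 says "Significant new findings that begin or worsen after informed consent must be recorded on the Adverse Event eCRF page", with no grade limit.

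On what ICG does, section 0.1.0 says "Overall adverse reaction to systemic ICG is estimated to be around 5% with only 0.05% as serious adverse reactions" and "The most common adverse reactions include nausea, extravasation of ICG and urticaria". Section 9.3.0 describes the most frequent reactions as allergic, with nausea or hypotension. Neither section gives CTCAE grades.

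**The concern.** The study intervention is only the ICG injection and the imaging (section 0.0.1). The surgery is standard care. The AE rule keeps all severe surgical complications and drops every non-serious event below grade 3, so the AE tables will mostly describe the pancreatectomy. Section 12 puts no figure on this for the trial, but the background gives 47% morbidity for distal pancreatectomy against 5% for any ICG reaction.

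Two things are at stake. First, a table headed as all on-study or treatment-related AEs could show no ICG reactions chiefly because lower-grade ones were never written down, and its label would not tell the reader so. Second, the protocol commits to reviewing adverse effects of ICG at the interim and to having evaluated ICG safety at the end, while its own rule removes many of the observations on which either would rest.

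**Working it through.** The protocol gives no figure for this point that could be reproduced, so the check is a comparison of the passages and then a calculation from the protocol's own rates.

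**Do the passages fit together?** Under sections 7.0.5 and 9.4, the record holds grade 3, 4 and 5 events and any SAE of lower grade. In section 10.3.3, the all-grade summary and its grade 3-4 counterpart would then differ only by deaths and by SAEs below grade 3; the same holds for the treatment-related pair. Listing them separately makes sense mainly if grades 1-2 are collected. Section 7.0.3 would put a significant grade 2 finding on the AE page that section 7.0.5 keeps off it.

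**How many ICG reactions would be seen?**

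Inputs:
- any ICG reaction, 5% per patient; serious reaction, 0.05% per patient (section 0.1.0)
- n = 15 at the interim review and n = 50 at the end (section 2.0)
- share of ICG reactions that are grade 3 or higher: not stated. Assumed range 1% to 20%, that is 0.05% to 1% per patient. The lower end uses the serious rate as a proxy; the upper end has no source in the protocol.

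Share of reactions that are non-serious: 1 − 0.05/5 = 99%.

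Formulas: expected count = n × p; chance of at least one = 1 − (1 − p)^n.

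| What is recorded | p | Expected, n = 15 | At least one, n = 15 | Expected, n = 50 | At least one, n = 50 |
| --- | --- | --- | --- | --- | --- |
| Current rule, 1% of reactions grade 3+ | 0.0005 | 0.0075 | 0.75% | 0.025 | 2.5% |
| Current rule, 10% grade 3+ | 0.005 | 0.075 | 7.2% | 0.25 | 22.2% |
| Current rule, 20% grade 3+ | 0.01 | 0.15 | 14.0% | 0.5 | 39.5% |
| All grades | 0.05 | 0.75 | 53.7% | 2.5 | 92.3% |

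Example, all grades at 15: 1 − 0.95^15 = 0.537. Example, 20% grade 3+ at 50: 1 − 0.99^50 = 0.395.

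The chance of a zero count is the complement. At 50 patients it is 60.5% to 97.5% under the rule and 7.7% with all grades. At 15 it is 86.0% to 99.25% under the rule and 46.3% with all grades.

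**What could the interim show even with full collection?** Zero reactions in 15 leaves a one-sided 95% upper bound of 1 − 0.05^(1/15) = 18.1%. Zero in 50 leaves 1 − 0.05^(1/50) = 5.8%.

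**The case against.** The omission is deliberate. It is stated twice with a reason, for an approved drug, and safety is not among the objectives in sections 1.0 and 1.1. The named pause triggers in section 9.6 are grade 4 toxicity and death, which the rule captures. One can also read the all-AE label in section 10.3.3 as all recorded AEs, and section 7.0.3 as a general rule that the specific ones override. All of this is fair, and it makes the threshold itself defensible. It does not make the threshold fit the interim review, the expected outcome or the table list as written.

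Three stronger readings are tempting, and the protocol does not support them.

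- A reader might infer that the safety review will have almost no data. It will still have all-cause grade 3+ events, SAEs, unanticipated problems and continuous vital signs during injection. What is thin is the information on ICG reactions.
- A reader might infer that the common ICG reactions are grade 1-2 on the protocol's own scale. The protocol does not grade them. Serious is not the same as grade 3, hypotension and allergic reactions may be severe, and the scale printed in section 9.1.3 applies only where CTCAE has no grading.
- A reader might infer that collecting all grades would let the 15-case review detect an excess. With 0.75 reactions expected and an 18.1% upper bound on a zero count, it would not do so reliably.

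The 5% and 0.05% rates are also the protocol's estimates for systemic ICG in general. That they carry over to this setting is assumed.

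**Conclusion.** The inconsistency stands. Sections 7.0.5 and 9.4 exclude events that sections 2.0, 7.0.3 and 10.3.3 presuppose. Taking the protocol's rates as given and assuming 1% to 20% of ICG reactions are grade 3 or higher, the rule cuts the chance of recording any ICG reaction from 92% to between 2.5% and 39.5% over the whole trial, and from 54% to between 0.75% and 14% at the interim. A zero count would largely reflect the rule; at 15 patients the small number contributes as well.

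This does not show that the trial is unsafe or that its objectives fail. It is a worthwhile and cheap correction, and what it buys is an honest description of ICG reactions.

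**What to change.** In sections 7.0.5 and 9.4, keep the grade 3 threshold for events not attributed to ICG. Add that ICG-attributed reactions of any grade (for example hypersensitivity or rash, hypotension at injection, extravasation) are recorded during surgery and in the immediate postoperative period, with the number of ICG doses and the total mg given. Use these records in the interim safety review and in the treatment-related tables. In section 10.3.3, relabel the overall table as *all collected AEs* and state the threshold. Bring the sentence in section 7.0.3 into line.

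If the sponsor prefers not to collect more, the minimum is to restrict the interim review and expected-outcome wording in section 2.0, the recording sentence in section 7.0.3 and the tables in section 10.3.3 to grade 3+ AEs and SAEs.

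The cost is a short checklist on the day-of-surgery form. Study staff are already in the operating room and already record repeat doses (section 5.0.7), and vital signs are monitored continuously during injection (section 5.0.8). About 2.5 true ICG reactions are expected in 50 patients. A few mild events of uncertain cause will be added, because the possibly-related category in section 9.1.4 asks only for some evidence; the short window limits their number.
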